## Abstract

**Background:**

The misuse of and addiction to opioids is a national crisis that affects public health as well as social and economic welfare. There is an urgent need for strategies to improve opioid use disorder treatment quality (e.g., 6-month retention). Substance use disorder treatment programs are challenged by limited resources and a workforce that does not have the requisite experience or education in quality improvement methods. The purpose of this study is to test a multicomponent clinic-level intervention designed to aid substance use disorder treatment clinics in implementing quality improvement processes to improve high-priority indicators of treatment quality for opioid use disorder.

**Methods:**

A stepped-wedge randomized controlled trial with 30 outpatient treatment clinics serving approximately 2000 clients with opioid use disorder each year will test whether a clinic-level measurement-driven, quality improvement intervention, called Coaching for Addiction Recovery Enhancement (CARE), improves (a) treatment process quality measures (use of medications for opioid use disorder, in-treatment symptom and therapeutic progress, treatment retention) and (b) recovery outcomes (substance use, health, and healthcare utilization). The CARE intervention will have the following components: (1) staff clinical training and tools, (2) quality improvement and change management training, (3) external facilitation to support implementation and sustainability of quality improvement processes, and (4) an electronic client-reported treatment progress tool to support data-driven decision making and clinic-level quality measurement. The study will utilize multiple sources of data to test study aims, including state administrative data, client-reported survey and treatment progress data, and staff interview and survey data.

**Discussion:**

This study will provide the field with a strong test of a multicomponent intervention to improve providers’ capacity to make systematic changes tied to quality metrics. The study will also result in training and materials that can be shared widely to increase quality improvement implementation and enhance clinical practice in the substance use disorder treatment system.

**Trial registration:**

Trial #NCT04632238NCT04632238 registered at clinicaltrials.gov on 17 November 2020

Contributions to the Literature
We will advance the literature on the implementation of quality improvement practices by testing whether a multicomponent intervention improves high priority targets for quality measurement in substance use disorder treatment (e.g., 6-month retention in care).We will make a novel contribution to the literature by testing whether incorporating a technology-based client-reported treatment progress tool (the Treatment Progress Assessment-8) supports data-driven clinical decision making and clinic-level quality measurement and improvement.We will extend the external facilitation literature by adapting the Integrated Promoting Action on Research Implementation in Health Services (i-PARIHS) framework to implement quality improvement practices in substance use disorder treatment programs.

## Background

The misuse of and addiction to opioids is a national crisis that affects public health as well as social and economic welfare. Data from 2018 shows that 128 people in the USA died every day from opioid overdoses and approximately 2 million people had opioid use disorder (OUD) [1]. The opioid epidemic has strained the healthcare and substance use disorder (SUD) treatment systems. For example, from 2010 to 2017, OUD-related hospitalizations increased by 54% and emergency department visits increased by 109% [2]. During this same time, admissions to SUD treatment programs for opioid use grew by 42% [3]. The current COVID-19 pandemic has caused additional concern due to anticipated increases in opioid use and overdose deaths as well as decreases in treatment access [4–10].

Multiple systematic reviews have concluded that SUD treatment in the USA has large gaps in quality of care and limited capacity for systems-level improvement [11–16]. These reviews and other studies highlight a number of systemic issues in the SUD treatment system, including (1) too few with an SUD have access to treatment, (2) treatment is often not evidence based, and (3) poor treatment completion and retention rates among those who do access treatment [17–19]. These quality gaps could be partially due to the SUD treatment workforce traditionally having limited professional education and training to provide scientifically supported practices or engage in quality improvement (QI) initiatives to change clinical outcomes [11, 14, 15]. Further, clients cite lack of flexibility and care that is not person-centered as reasons for dissatisfaction and lack of engagement in treatment [20–23]. Additionally, there have been few financial incentives to drive innovation among SUD treatment programs.

As a result of the issues described above, there have been consistent calls for new payment models that link payments to measures of quality instead of fee-for-service payment models that reward volume [11, 14]. In order to transition to such payment models, programs must incorporate or improve evidenced-based practice offerings, offer more person-centered approaches, become more data and outcome-driven, implement QI programs, and expand the use of technology [13, 24–27]. Yet, there is deep concern that SUD treatment programs cannot survive this transition and may need a great deal of support to improve their clinical and business operations [28, 29]. Therefore, the workforce could benefit from training on evidence-based practices and person-centered care, new tools to better monitor client treatment outcomes, and support to implement QI protocols.

There is limited research on how to best guide SUD treatment programs in implementing systematic QI processes [30, 31]. Challenges to implementing QI protocols in SUD treatment programs include non-prioritization of data collection, limited analytical capacity, poor IT systems, and lack of data-driven decision-making culture [32, 33]. Qualitative research has found that SUD treatment staff need basic training on data collection and use [34]. One of the most studied approaches to QI in SUD treatment, the Network for Improvement of Addiction Treatment (NIATx), emphasizes identifying key problems, engaging change leaders, and using a series of rapid cycle tests to make changes. While the NIATx approach has been shown to improve service provision in its targeted areas (i.e., wait times and retention), there are mixed results for other outcomes (e.g., increasing admissions) [34–36] as well as criticisms, including the level of commitment required by staff, scarce resources to implement burdensome processes, detailed data requirements, and issues with long-term sustainability [30, 34, 37]. New strategies are needed to guide SUD treatment programs through implementing sustainable QI processes that build on lessons learned from previous research and that are tailored to existing resource and workforce limitations.

Utilization of data and metrics as well as implementation of QI processes will require SUD clinics to make significant changes at various levels within their organizations. This study will use an external facilitation model guided by the Integrated Promoting Action on Research Implementation in Health Services (i-PARIHS) framework to support clinic implementation of QI processes [38, 39]. i-PARIHS posits that optimal implementation occurs when practice facilitation promotes the acceptance and use of a new innovation by tailoring it to the recipient’s specific needs [39, 40]. Facilitators are the active ingredient that help navigate teams through complex change processes by addressing (a) the fit within the existing clinic, (b) motivations, beliefs, goals, and resources of intervention recipients, and (c) the inner and outer implementation context. In QI projects, the goal of facilitation is typically to support sustained focus and achievement of specific goals; facilitators work to enable individuals and teams to analyze, reflect, and change their way of working [41].

Patient monitoring tools are central to managing quality of care for other behavioral health conditions yet are not often systematically used in SUD treatment programs. For example, a hallmark of collaborative care models for depression is the use of evidence-based assessment tools, like the PHQ-9 depression scale, for ongoing monitoring and treatment adjustments. We recently developed an 8-item tool for SUD clinic settings, the Treatment Progress Assessment-8 (TPA8), that monitors SUD symptoms and treatment progress indicators that are associated with clinical outcomes and relapse [42]. We have been in the process of developing an electronic version, the eTPA8, to ease administration to clients as well as to provide a robust data reporting system that SUD clinics can use in client care as well as QI efforts. The eTPA8 will be part of the intervention package in the current study to support QI practices.

In this paper, we describe a study protocol for a stepped-wedge randomized controlled trial (SW-RCT) stemming from a state-academic partnership that will test a multicomponent, clinic-level intervention, called Coaching for Addiction Recovery Enhancement (CARE). We will test whether CARE improves treatment process quality and recovery outcomes over treatment as usual, particularly for OUD. The SW-RCT design was selected mainly because the intervention is conducted at the clinic-level and, from a resource perspective, it would be impractical to provide the intervention to all clinics at once given the facilitation model being utilized. Further, the stepped-wedge design was seen as more acceptable and ethical for key program stakeholders (notably the single state agency that regulates SUD treatment [SSA]) due to the potential benefits from the resources being provided as part of the intervention package (e.g., training support from the SSA) compared to a parallel randomization design. The CARE intervention includes the following components: (1) staff clinical training and tools, (2) quality improvement and change management training, (3) external facilitation to support implementation and sustainability of quality improvement, and (4) the eTPA8 client-reported treatment progress tool to support data-driven decision making and clinic-level quality measurement. See Fig. 1 for our intervention conceptual model. We describe intervention components in more detail in the method section. Study aims and hypotheses are the following:
Aim 1: Test the effect of CARE on treatment process quality measures and recovery outcomes.
Hypothesis 1: CARE will improve clinic-level rates of treatment process quality measures (i.e., initiation of and adherence to OUD medications, in-treatment symptom and therapeutic progress, 6-month treatment retention) and recovery outcomes (i.e., substance use, overdoses, self-reported health status, hepatitis C infection [HCV], and emergency department [ED] visits).Aim 2: Examine association of changes in the eTPA8 client-reported treatment progress tool with treatment retention and substance use outcomes.
Hypothesis 2: Positive change in the eTPA8 scale will be associated with longer retention and reduced substance use at follow-up.Aim 3: Examine whether there are program admission changes in terms of client complexity (e.g., homelessness, psychiatric conditions) to test impact on client access (i.e., adverse selection) as clinics monitor quality measures.
Hypothesis 3: Clinic rates of severe OUD (i.e., daily use and/or injection use), homelessness and psychiatric conditions at admission during the year following the CARE intervention will decrease from baseline rates.Aim 4: Examine staff attitudes, experiences, and behaviors related to (1) implementing the eTPA8 and clinical practice change, and (2) working with external facilitators to implement QI processes.Aim 5: Estimate addiction program and state intervention costs of CARE and impact on Medicaid costs.

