## Method/design

### Design and participants

We will employ a SW-RCT with 30 outpatient SUD treatment clinics who serve approximately 2000 clients with OUD per year to test whether CARE improves treatment process quality and recovery outcomes over treatment as usual. The study will benefit from multiple sources of data to test study aims, including state administrative data, client-reported survey and eTPA8 data, and staff interview and survey data. Therefore, this will be a robust study of the implementation of a measures-driven QI approach for SUD treatment. Figure 2 shows the stepped-wedge design. Five clinics will start CARE every 6 months over 3 years; therefore, there are 6 steps, each with 5 clinics randomly assigned to 1 of the 6 steps.

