### Measures and materials

#### Data sources

The NYS OASAS registry of all admissions and discharges (irrespective of payer) to licensed addiction treatment facilities—the Client Data System (CDS)—forms the basis of our administrative data set. The CDS will record all treatment episodes that occur in the 30 clinics we include in this study, providing a rich source of data. All licensed providers of SUD treatment in NYS are mandated to submit admission and discharge data into the CDS. NYS OASAS tracks each individual by unique identifiers. When clients enter treatment, providers enter information on demographics, level of functioning (e.g., health status, comorbidities), criminal justice status, recent history and frequency of substance use, and recent SUD treatment history. Upon discharge, providers enter information on functional status (e.g., employment, housing), source of payment for treatment (e.g., self-pay, Medicaid, private insurance), criminal justice involvement during treatment, hospitalizations, and use of ED services. Additionally, the discharge information has type, frequency (i.e., number of sessions), and intensity of SUD treatment as well as discharge status (discharge disposition and goal achievement). NYS Medicaid claims will supplement the administrative dataset by providing data on OUD medications and health services use (e.g., ED visits). We will link clients in Medicaid to the CDS using the NYS OASAS identifier augmented, in cases where there were no exact matches, by searching for same treatment events that were recorded in each database. Additionally, we will employ probabilistic matching techniques to account for data entry errors on elements of the OASAS identifier. Our link rate in previous studies among OUD individuals in Medicaid is 90% [47].

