### Analysis and power

The primary aim of this study is to test whether CARE is associated with greater use of pharmacotherapy for OUD, longer retention in care, and improved recovery outcomes (e.g., reduced drug use). We will employ multiple convergent analytical methods to (a) examine CARE implementation and (b) test association between CARE and OUD treatment outcomes. Analyses will begin with examination of distributions of variables and transformations where appropriate, examination of patterns of missingness, and application of formal imputation methods [77–79] if deemed essential to project aims. Analyses for Aims 1, 2, and 3 will utilize general linear mixed models (GLMM) for stepped-wedge designs [80–85]. For example, to test the effect of CARE on treatment process quality measures (i.e., initiation and adherence to OUD medications, in-treatment symptom and therapeutic progress, 6-month treatment retention) and recovery outcomes (substance use, overdoses, self-reported health status, HCV infection, and ED visits), we will employ stacked difference-in-difference models that test for within and across clinic changes while adjusting for secular trends across time [80, 86, 87]. The models will take the form: *Y*_*ikt*_ = *μ* + *X*_*kt*_*θ* + *β*_*t*_ + *Z*_*ikt*_ + *α*_*k*_ + *e*_*ikt*_, where *β*_*t*_ is a fixed effect for time, *Z*_*ijk*_ is a matrix of covariates measuring individual, geographical, and clinic characteristics for person *i* in clinic *k* at time *t, X*_*kt*_ is an indicator for intervention in clinic *k* at time *t* (coded 0 for baseline then 1 from when intervention begins in clinic through end of study), and *θ* is the treatment effect. *Y*_ikt_ represents a matrix of binary variables: treatment process quality measures (i.e., pharmacotherapy initiation and adherence, in-treatment symptom and therapeutic progress, treatment retention) and recovery outcomes (i.e., substance use, overdoses, self-reported status, HCV infection, and ED visits). We will estimate the effect of CARE (*θ*) while controlling for secular trends (*β*) and adjusting for clustering within clinic (*α*_*k*_) using robust standard errors. We will also conduct a set of falsification tests. These will include (1) testing for variation in program and client characteristics across time of enrollment; (2) examination of variation across study time in the study outcomes for clinics not participating in the study; and (3) examination of variation in intervention effect based on clinics’ baseline levels of quality measures (e.g., comparing top third to bottom third in quality of care at baseline).

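### Aim 3's share of complex clients among admissions measures case mix, but alone it cannot support a conclusion about client access

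*Protocol article*

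**What the plan says.** In the Background of the protocol article, Aim 3 looks at changes in the complexity of admitted clients "to test impact on client access (i.e., adverse selection) as clinics monitor quality measures". Hypothesis 3 names the measure, "Clinic rates of severe OUD (i.e., daily use and/or injection use), homelessness and psychiatric conditions at admission", and the expected result: these rates "during the year following the CARE intervention will decrease from baseline rates".

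Analysis and power assigns the method: "Analyses for Aims 1, 2, and 3 will utilize general linear mixed models (GLMM) for stepped-wedge designs". The model there is written for person i in clinic k at time t, so only people who were admitted contribute data.

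No count of admissions, total or complex, is named as an Aim 3 outcome. Under Measures, annual census is listed only as a provider covariate. The first falsification test in Analysis and power looks at how program and client characteristics vary over time, which is not a test of volume.

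The data for counts are already there. Data sources describes the Client Data System (CDS) as "The NYS OASAS registry of all admissions and discharges (irrespective of payer) to licensed addiction treatment facilities" and adds: "The CDS will record all treatment episodes that occur in the 30 clinics we include in this study".

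**The concern.** Aim 3 guards against an unintended harm: clinics that are coached on quality measures might take fewer clients with severe OUD, homelessness or psychiatric conditions. The stated purpose is access, but the measure is composition. The two agree only while the number of other admissions stays put.

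If total volume moves during the trial, the share can mislead about access in two ways. It can fall because more low-complexity clients were admitted, and Hypothesis 3 would then look supported with nobody turned away. It can also stay level while every group shrinks, which could be reported as access preserved. The Background frames this work around payment tied to quality measures, so a false alarm or false reassurance about access for these clients would matter to those who use the result.

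**Working it through.** The article gives no baseline share, power or expected change for Aim 3, so there is no figure to reproduce. The check is an identity with illustrative numbers.

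**Inputs**
- Volume: "30 outpatient SUD treatment clinics who serve approximately 2000 clients with OUD per year" (Design and participants). 2000/30 = 66.7 per clinic-year, or 33.3 per clinic per 6-month window. Assumption: clients served stand in for admissions.
- Baseline share of complex clients: not given. Assumption: 30%, with a range of 20% to 50%.
- Size of any volume change: not given. All values below are assumptions.

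**Formula.** Let C be complex and L low-complexity admissions. The share is s = C/(C + L). Multiplying C and L by the same factor leaves s unchanged; raising L with C fixed lowers s.

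**Per clinic-year, at 30%: C = 20.0, L = 46.7**

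| Change | Complex count | Share |
|---|---|---|
| None | 20.0 | 30.0% |
| L +10% | 20.0 | 20/(20 + 51.3) = 28.0% |
| L +20% | 20.0 | 20/(20 + 56.0) = 26.3% |
| L +30% | 20.0 | 20/(20 + 60.7) = 24.8% |
| C and L both −20% | 16.0 | 16/53.3 = 30.0% |
| C −20%, L −30% | 16.0 | 16/(16 + 32.7) = 32.9% |
| C +10%, L +30% | 22.0 | 22/(22 + 60.7) = 26.6% |

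In the last two rows the share moves in the opposite direction to complex-client admissions.

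**Range.** For baseline shares from 20% to 50%, L +30% lowers the share by 3.9 to 6.5 percentage points with no complex client lost. A 20% fall in everything leaves the share unchanged, with 2.7 to 6.7 complex clients lost per clinic-year. At 30% the loss is 4.0 × 30 clinics = 120 a year.

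**What counts could show.** At a 30% share there are 10 complex admissions per clinic-window. Comparing two windows with two windows over 30 clinics gives 10 × 2 × 30 = 600 at baseline. Under simple Poisson variation:
- 20% fall: ln(480/600)/√(1/480 + 1/600) = −0.223/0.0612, so z = −3.64.
- 8% fall: ln(552/600)/√(1/552 + 1/600) = −0.083/0.0590, so z = −1.41.

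The 8% is the only volume change that can be tied to the plan's own figures. Analysis and power takes retention from 25% to 27.8%. If stays are exponential, mean stay lengthens by ln(0.25)/ln(0.278) = 1.083. At a fixed caseload, admissions fall to 1/1.083 = 0.92 of their former level. Exponential stays and a fixed caseload are both assumptions; the article states neither.

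**The case against.** The strongest reply is that the article narrows access to adverse selection. Selection concerns who is admitted, and case mix at admission measures that directly. If all admissions fall by 20%, no selection has taken place and a flat share is the right answer. This stands for selection in the narrow sense, so the missed-loss half of the point bears on the wider stated purpose of impact on client access. The dilution half bears on both, because a lower share does not show that complex clients were turned away.

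Second, the volume shifts are invented. CARE's stated targets are medication use, retention and recovery outcomes, not admissions, and no capacity limit is given. The Background's mention of mixed results on admissions concerns a different quality improvement approach. This also stands: the size of any distortion is unknown.

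Third, counts have faults of their own. A share cancels shocks common to both kinds of client; a count does not, and the Discussion describes large COVID-era disruption to services. A clinic that expands by taking only easier clients while complex demand also grows would show a flat count although selection had occurred. At an 8% fall the count would probably miss the loss as well. For these reasons a reader might infer that the share is the wrong outcome and should give way to counts, or that any conclusion from it must be false. The documents do not support either inference.

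Fourth, the article is condensed and does not spell out the denominator of the clinic rates. A share among admissions is the natural reading and fits the person-level model, but it remains a reading. Raw numbers may well be reported beside the rates. What the article fixes, though, is a hypothesis about rates alone for an aim about access, and that goes beyond a reporting detail.

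**Conclusion.** The point holds in a limited form. The share is a valid case-mix outcome for Aim 3, but it cannot carry an access conclusion alone: a lower share does not show that complex clients lost access, and a flat share does not show that access was kept. The direction is an identity and holds at any baseline share. The illustrative size, 30% falling to about 25% with no complex client lost, rests on an assumed baseline share and an assumed 30% rise in low-complexity admissions. Nothing in the article shows that such a shift will occur. The primary aim is unaffected. This is a cheap improvement to what Aim 3 can conclude.

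**What to change.** Keep the share as the case-mix (selection) outcome. Add two co-reported Aim 3 outcomes from the CDS, per clinic per 6-month window: the number of admissions with severe OUD, homelessness or a psychiatric condition, and total admissions. Analyse them with a log-link count model that allows overdispersion, with clinic and calendar-window effects and the same intervention indicator.

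State the reading rule in advance:
- Conclude that access was lost only if complex-client counts fall.
- Describe a lower share with stable complex-client counts as a case-mix shift.
- Do not read a flat share as preserved access without the counts.

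Cost: a sentence or two in Hypothesis 3 and one extra model, with no new data collection. The counts will be overdispersed, so the Poisson z values above are optimistic. They are exposed to COVID-era swings in volume; calendar-window effects remove only what is common to all clinics. Power for small changes is low (about z = −1.4 for an 8% fall), so a null count result should be reported with its interval and not as evidence of no loss.
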